### 2.2. Objectives and Hypothesis

The main objective of this study protocol is to improve the cognitive performance and emotional competence of students at risk of social exclusion in vulnerable areas of Guatemala (due to their high exposure to violence and low socioeconomic level) and consequently improve their academic performance, psychological adjustment, and quality of life. The specific objective is the development of a comprehensive neuropsychological stimulation program in which the following cognitive and emotional functions are targeted: attention, language, executive functions, social cognition, and emotional competence. This comprehensive intervention responds to the needs identified in our previous studies, and we hypothesize that strengthening cognitive abilities and emotional competence will improve overall health and well-being, as previous studies have shown [25,26,27].

### 2.3. Instruments

#### 2.3.1. Comprehensive Assessment Battery

To obtain the baseline data of the participants and evaluate their subsequent cognitive and emotional performance after the intervention, we will use a battery of neuropsychological tests to assess the cognitive domains of language [36,37,38]: attention [39], executive functions [40,41,42,43,44], and social cognition [45]. We will also assess their mental health [46,47], emotional management [48], and quality of life [49]. Lastly, we will take measurements of their family’s socioeconomic level, clinical history, food consumption [50], exposure to violence [51], and academic performance (for detailed explanations of the assessment instruments, see Supplementary Materials). In total, there will be four assessment sessions, each lasting between 45 and 60 min. The session plan has been designed in a modular way that allows for flexible administration in order to accommodate participants who cannot attend the educational centre on a daily basis. Each module can be assessed in any order, and they can be applied one after the other within the same session (providing breaks in between), although assessing each module on different days would be ideal. Given the large number of tests that will be required for a comprehensive assessment, it will become difficult to compare results across tests. For this reason, converting results to percentiles or z-scores will need to be performed in order to make meaningful comparisons between instruments.

#### 2.3.2. Cognitive and Emotional Intervention Program

The intervention program will be carried out using tablets with access to the digital neurorehabilitation platform NeuronUP [52], a tool for neuropsychological rehabilitation, stimulation, and session management tool [53,54,55]. Computerized neuropsychological interventions are an alternative to the classic pencil and paper tasks that offer patients a novel and entertaining way to train their cognitive skills. These interventions have been internationally validated [56,57,58,59,60,61]. The sessions themselves will be divided into 30 min of stimulation time and 15 min for distributing the tablets at the beginning, logging in to the students’ accounts, and collecting them at the end. Since the stimulation program will be carried out through the use of this app, there are no associated health risks for the participants; it is a non-invasive method of cognitive stimulation prepared to promote participant engagement and reduce frustration by presenting exercises as mini-games. The sessions will be programmed by specialists in neuropsychology from the research team using the NeuronUP2GO functionality, an online application that allows for managing the stimulation sessions of users located anywhere around the world. Remote monitoring provides continuous control, thanks to the fact that all activities and results are stored on the platform itself. In addition, using NeuronUP2GO, professionals can adapt sessions based on the progress of each user, thus achieving a controlled and personalized intervention. The stimulation program will aim to train the participants in activities targeting attention, language, executive functions, and social cognition in a cyclical manner, dedicating each day to a specific domain. Activities will be different in every session to avoid boredom. However, they will be training the same cognitive domains, so participants are able to work on improving them at a similar pace. The program will also have three levels of difficulty (easy, medium, and hard) that will increase in difficult every two cycles, so the students have time to adapt to their current difficulty level without being rushed. There will be two activities for each cognitive skill at every difficulty level (see Figure 1). 

This also makes it possible to apply the program in a flexible way to entire class groups in which there are usually small differences in age as well as different rates of development and special needs. Additionally, it allows children who take longer to adapt the time they need to develop the intended capabilities gradually, while providing every child the same level of stimulation, so the whole class can keep steady progress. The administration of tablets to participants in each session will be carried out by personnel, duly trained and appointed by the management team of the educational centres (normally academic tutors or those responsible for the computer area), with periodic supervision by neuropsychology and educational psychology specialists from the project in case any problems or questions arise. The first session will include an initial presentation in which professionals instruct participants on how to operate the tablets and the app, making it slightly longer than other sessions. A pilot trial has already been carried out with Guatemalan children from these schools to adapt the activities culturally and linguistically. A team of Guatemalan and Spanish neuropsychology experts and native teachers reviewed children’s feedback from this pilot and, with the help of NeuronUP staff, made necessary adjustments to the activities selected for the program to ensure cultural and linguistic adaptation for Guatemalan children.

There are several benefits that the intervention may bring to participants. They will engage in around one hour per week of digital exercises created to stimulate and strengthen cognitive functions and emotional management. These functions are essential for proper child development and have a significant impact on their social and academic performance. It is important to outline the fact that this study will not have a passive control group, as it is part of a bigger international cooperation project conducted by the founding organization focused on providing health and educational services to vulnerable populations, requiring all children to receive some kind of intervention. The control group will use the time dedicated for intervention sessions to carry out a reading motivation program that is regularly used in these schools (a “therapy as usual” control group). This program has been proposed by Fe y Alegría to train reading proficiency while exploring a variety of topics, such as gender equality, sexuality, and many other social topics. They will also perform regular academic activities that the responsible teaching staff consider pertinent. 

This study will contribute to improving the living conditions of Guatemalan children through innovative actions designed to respond to the specific needs of children in vulnerable contexts. Initially, the previous study on socioeconomic status and cognitive development has allowed us to identify the areas that need greater reinforcement [21]. Therefore, the exercises developed using tablets, which have already proven to be successful in other contexts, will be adapted to the needs of the group with which we will work. In addition, the previous study has found anxiety and depression symptoms that are higher than expected and higher than the average, especially in urban–marginal sectors. For this reason, actions to strengthen emotional intelligence are included. Evidence shows that, in addition to improving concentration and academic performance, this type of intervention promotes the prevention of the appearance of violent, addictive behaviours, and other behaviours associated with impulsiveness and difficulty in long-term planning, thus contributing to personal and collective empowerment of these children [27,29,30].

### 2.4. Procedure

The design of this study protocol follows the guidelines of the CONSORT-revised recommendations for improving the quality of reports of parallel group randomized trials [62]. The study has been pre-registered with the Open Science Foundation. Ideally, children should be randomly allocated to either the control or the experimental group. However, implementation of this protocol requires the use of at least two rooms at the same time, along with a high level of logistical organization in terms of moving the children to their correct rooms for each session. Given the nature of the schools involved, we do not believe it is realistic to expect that these resources will always be available. Hence, we propose that the study will be carried out through a multicentre randomized controlled trial in which entire classes of children will be assigned to either the control or experimental conditions. We note, however, that the members of each class are allocated at random by the school as they enroll, so in this sense, random allocation at the participant level is still somewhat achieved. To minimize potential bias related to school-specific factors, each school will provide [at least] two classes, thus ensuring that each school is represented in both conditions. Efforts should be made to ensure as close to a 1:1 ratio of students between groups as possible. The class designated as the experimental group will receive the intervention. The second group will be made up of the students who will form the control group. A crossover design will be used in which the role of each group is reversed during the following academic year, thus ensuring that each child has the opportunity to benefit from the intervention program. The study will therefore be divided into two blocks (see Figure 2). The first block will occur in year 1 and will consist of a prior and posterior assessment (T1 and T2) of the children’s cognitive and emotional abilities and the implementation of the intervention program in between. The second block will occur in year 2 and will consist of a second intervention, followed by a final assessment (T3), which will occur when the children are in the 6th grade. In this block, the control and experimental groups will change roles. Apart from ensuring that all children may benefit from the intervention program, it will provide an opportunity to determine if there is maintenance of the benefits obtained by the experimental group during the first block. All assessments will be carried out by professional neuropsychologists and educational psychologists, duly trained to administer the assessment tasks by the experts from the research team.

The program will take place during the second half of the academic year, at a rate of two sessions per week, with an estimated duration of about 45 min per session. Participants will complete the two weekly sessions on different days of the week, depending on the school they attend, but always with at least one rest day in between. If, for some reason, there are participants who miss one of the sessions, they would have to recover it during the same week to avoid the risk of falling behind their classmates. If participants miss a session and cannot recover it within the same week, they will skip that session and continue with the normal session planned for the following week, but the missed session will be registered as lost. The justification for this decision is that sometimes access to schools or a stable internet connection will not be guaranteed in the context of the study. Hence, this protocol will prevent participants from lagging behind their classmates and avoids having participants completing different sessions in the same classroom. An additional reason for making this decision is that at the end of the program, we will be able to analyze the percentage of completion for each participant and determine the minimum completion percentage to ensure the program’s effectiveness. 

One advantage of the group sessions is that many children can benefit from professional intervention without the need to have one therapist for each child. Nevertheless, children with a previously diagnosed condition are at risk of greater disadvantage compared to their counterparts and may need specialized, one-on-one attention. We do not propose that these children be excluded from the intervention. However, with the help Fe y Alegría, an alternative intervention will be offered to families that wish to receive additional support by referring them to specialized services offered for people with limited economical possibilities. Furthermore, teachers will be provided with training to effectively aid and support these students within the school. 

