## Abstract

Background: Guatemala remains one of the poorest countries in Central America and suffers from high rates of social inequality and violence. In addition to the negative impact that two years without attending school has had on Guatemalan children due to the consequences of the COVID-19 pandemic, this unfavourable socioeconomic context poses a risk to children’s emotional and cognitive development. This work presents a protocol for implementing a cognitive and emotional stimulation program aimed at increasing the academic performance of these children and consequently improving their quality of life. Methods: The protocol proposes the implementation of a randomized controlled trial to assess the efficacy of a 24-session-long stimulation program. It targets the cognitive functions of attention, language, executive functions, and social cognition, using the digital neurorehabilitation platform NeuronUP. The participants (*n* = 480) will be randomly assigned to an Experimental or Control group. Pre- and post-intervention assessments will be carried out, together with a follow-up in the next academic year, in which both groups will change roles. Results will be compared for the first and second years, looking for differences in academic and cognitive performance between groups. Discussion: Mid- and long-term outcomes are still unknown, but effective interventions based on this protocol are expected to facilitate the following benefits for participants: (1) improved cognitive and emotional development; (2) improved academic performance; (3) improved well-being. We expect to create a validated neuropsychological stimulation program that could be applied in similar socioeconomically disadvantaged contexts around the world to help these children improve their life chances.

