Since all children will receive the intervention, we want to explore the effects this program may have on the children who do not meet the inclusion criteria but usually have special educational needs. Due to the nature of the intervention, it is impossible to implement it in a manner that allows both participants and the personnel administering the intervention to participate blindly. However, the personnel from the research team assessing the data will be blinded to group assignment to ensure as much of an unbiased outcome as possible. The interpretation of the data will also have to consider the group assignment to conclude the efficacy of the program.

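### The abstract promises random assignment of participants, but the Procedure allocates whole classes with no stated random class-to-arm step, relying on school enrolment and an open-ended effort towards 1:1 student numbers

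*Protocol article*

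**What the plan says.** The Abstract states that the 480 participants "will be randomly assigned to an Experimental or Control group".

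Section 2.4 (Procedure) describes something else:

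- Individual randomisation is an ideal: "Ideally, children should be randomly allocated to either the control or the experimental group". It is then set aside because rooms and logistics may not allow it.
- The design becomes a "multicentre randomized controlled trial in which entire classes of children will be assigned to either the control or experimental conditions".
- Randomness is attributed to enrolment and described as achieved to some degree: "the members of each class are allocated at random by the school as they enroll, so in this sense, random allocation at the participant level".
- Both arms appear in every school: "each school will provide [at least] two classes, thus ensuring that each school is represented in both conditions".
- Size balance is an aim: "Efforts should be made to ensure as close to a 1:1 ratio of students between groups as possible".
- The arm is then simply named: "The class designated as the experimental group will receive the intervention".

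Section 2.5 says of the intervention that "it is impossible to implement it in a manner that allows both participants and the personnel administering the intervention to participate blindly", while the research staff who assess the data are blinded to group. Section 2.3.2 adds that personnel appointed by school management, normally tutors or computer staff, run the tablet sessions.

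**The concern.** Two steps are being merged. The first is how children come to be in a class; the second is which class in a school gets the program. Section 2.4 describes randomness only in the first. Even if schools fill classes at random, classes can diverge afterwards through tutor, room, timetable and discipline. Only a random second step protects the comparison from those differences.

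The one instruction on class placement, beyond having both arms in each school, is an effort to equalise student numbers. Class sizes can be known before placement, and no limit says when the balance is good enough. The text therefore leaves room for the choice to follow class size or the judgement of people who know the classes. A class-level difference introduced this way would not shrink as more children are recruited, and adjustment for T1 scores would remove only part of it. Blinding the data assessors does not correct it.

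**Working it through.** **1. The plan's own sample size.** Section 2.1.3 gives d = 0.3 and a minimum of 352. Alpha and power are not stated; two-sided 0.05 and 80% are assumed. The normal approximation gives 175 per arm, 350 in total. The exact noncentral t gives 176 per arm, 352 in total, with power 0.801. The figure reproduces, and nothing here changes it.

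**2. Is a near-exact 1:1 ratio needed?** Exact-t power at N = 352 and d = 0.3, on the plan's individual-level calculation:

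| Arm ratio | Power |
|---|---|
| 1:1 | 0.801 |
| 1.25:1 | 0.797 |
| 1.5:1 | 0.785 |
| 2:1 | 0.754 |

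Moderate imbalance costs little, so there is little reason to let balance dominate the allocation.

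**3. How far does 'as close as possible' restrict the allocation if taken literally?** Section 2.1.2 gives five schools. Class counts and sizes are not given, so both are assumed.

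- Two classes per school: 2^5 = 32 within-school allocations. With 35 to 61 participants per class (mean 48 = 480/10), the median number reaching the smallest imbalance is 2, one split and its mirror image. With sizes of 36 to 60 the median is again 2 (5th to 95th percentile 2 to 8).
- Same layout, tolerance of 24 children (5% of 480): a median of 20 of the 32 remain (10th percentile 16). The worst permitted split is 252:228, a ratio of 1.11:1.
- Four classes per school, two per arm, 18 to 30 participants each: 6^5 = 7,776 allocations, of which a median of about 580 reach the smallest imbalance.

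The literal rule is severe in the two-class layout and much less so with more classes.

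**4. How large could the bias be if the choice were steered?** Take two classes per school, with independent normal class effects of variance ICC (total variance 1, after T1 adjustment). The expected gap between the better and the worse class is 2 × sqrt(ICC/π). Averaging over schools leaves it unchanged. If the better class is chosen with probability p, multiply by (2p − 1). The ICCs are assumed; the document gives none.

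| ICC | Better class always chosen | Chosen 75% of the time (× 0.5) |
|---|---|---|
| 0.02 | 2 × sqrt(0.02/π) = 0.16 | 0.08 |
| 0.05 | 2 × sqrt(0.05/π) = 0.25 | 0.13 |
| 0.10 | 2 × sqrt(0.10/π) = 0.36 | 0.18 |

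These are in residual SD. The plan's 352 matches a two-group test without a covariate, so d = 0.3 is in raw SD. With an assumed pre-post correlation of 0.7, the factor is sqrt(1 − 0.49) = 0.714, and the first column becomes 0.11, 0.18 and 0.25.

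**The case against.** A reader might infer that staff or class size decide the arms, or that the arms can be read off the class lists. The document supports neither. Section 2.4 calls the trial randomized, and the plain intention may be a draw of classes. The word 'designated' may only label a class after that draw. No sentence gives school staff a role in the choice, and a 1:1 target is compatible with restricted randomisation. Even where balance leaves one split and its mirror image, it fixes only which classes are grouped together. If the side is drawn at random, each class still has a 1/2 chance of either arm.

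The scenario is also uncertain. Section 2.4 asks for at least two classes per school, so the two-class layout is an assumption, and the restriction is far weaker with four. The full-steering figures require someone to pick, in every school, the class with the better residual outcome, which could hardly be known in advance. Several features help: both arms in each school, an active control, role reversal in year 2 (which weakens any motive to steer) and blinded data assessors. Who makes the draw and how it is concealed may stand in a full protocol that is not shown, so their absence from an article is no finding.

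All of this stands, and it limits the size of the point. It does not answer what the article states: the abstract and Section 2.4 disagree on what is randomised, the enrolment argument is mistaken, and the balancing instruction has no bound.

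**Conclusion.** The point holds as a fault in stated text. The Abstract claims random assignment of participants. Section 2.4 allocates classes, describes no random class-to-arm step, puts enrolment in its place, and adds an unstructured balancing effort. Selection of classes is therefore not ruled out; it is not shown to occur.

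The possible consequence is 0.16 to 0.36 SD against a target of 0.3. This is an upper bound, not a forecast: it assumes two classes per school, ICCs of 0.02 to 0.10 and the better class chosen in every school. Choosing it 75% of the time halves these figures, and on the raw-SD scale they are lower still. The matter should be settled before classes are assigned. Confidence is medium, because a full protocol may already specify a draw.

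**What to change.** In Section 2.4, replace the sentence on efforts towards 1:1 with a random draw of classes within each school. Someone independent of the schools makes it once class lists are final. Build balance in as a pre-set tolerance: list the within-school allocations, keep those whose arm totals differ by no more than, for example, 5% of participants (24 of 480), and draw one at random. The mirror image of every acceptable allocation is also acceptable, so each class keeps a 1/2 chance of either arm.

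Delete the statement that school enrolment supplies random allocation at participant level. Change the Abstract to say that classes within schools are randomised.

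The cost is a few sentences and a short program. The ratio may be slightly off 1:1 (at most 252:228), with negligible power loss: power stays between the 0.801 at 1:1 and the 0.797 at 1.25:1. Schools also give up any choice of class.

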Living conditions during childhood and adolescence affect the cognitive and emotional development of minors, resulting in important long-term effects in their adult life [11,12,13,14]. Existing literature on growing up in disadvantaged environments reports that language development, attention, and executive functions can all be affected. Additionally, experiencing these types of adverse contexts can also have a considerable negative impact on children’s social skills and emotional regulation [15,16,17,18]. The development of this study protocol arises from the need to respond to some of the problems discovered after the conclusion of a previous project [19]. Its goal was to improve existing neuropsychological assessment task scores for children and adolescents in Guatemala and study how different factors within their environment could affect their cognitive development. The results obtained in this previous study revealed that Guatemalan children and adolescents participating in the project needed effective support on multiple levels due to their situations of vulnerability. In this study, vulnerability was defined as belonging to an especially disadvantaged socioeconomic context, both in terms of poverty and direct exposure to extreme violence; this was the definition used in the previous study [20]. This showed that the hypotheses regarding the negative impact of growing up in disadvantaged socioeconomic environments (e.g., low educational level of caregivers, little intellectual stimulation in their environment, food insecurity) on the cognitive performance of children and adolescents were confirmed in this population [20]. Additionally, it was possible to detect a series of mental health difficulties in some of the participants that could not be left unattended. This included high levels of anxiety and depression, especially among children from urban areas with high rates of violence [21]. In summary, evidence indicates that living conditions during childhood and adolescence affect the cognitive and emotional development of children, having significant effects on their academic performance, which in turn tends to condition their long-term adult life [12,13,14]. Likewise, the stress associated with poverty causes a serious impact on the emotional and social development of these children, highlighting the urgent need to work in these areas [22,23]. 

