#### 2.1.3. Sample Size

To ensure that the size of the improvements realized by the intervention are of practical significance, we propose a minimum effect size of Cohen’s *d* = 0.3, which is a small-to-medium effect. A power calculation using this effect size and the proposed analysis plan (see below) was carried out using the program G*Power [35] and indicated that the minimum sample size we require for the study is n = 352. However, due to the difficult living conditions in the proposed recruitment areas (gang violence, long distances from residences to school centres, etc.), we expect a high dropout rate. Therefore, we propose to recruit a total of 480 children as this would allow for slightly more than 25% of the sample to stop participation in the study yet still allow us to maintain sufficient statistical power to detect the target effect size. Furthermore, the figure of 480 represents approximately one-third of 5th grade students attending Fe y Alegría Guatemala across their 46 centres. Thus, we would only need consent from one in every three children to achieve the necessary sample size. This sample size could be reduced if research teams were prepared to look for larger effect sizes. Furthermore, once this protocol is implemented, research groups should consider creating a contingency plan based on the specific conditions they encounter to address potential difficulties in recruitment.

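### Observed session completion is not randomised, so it cannot establish the minimum percentage that ensures the programme works; the analysis should be exploratory

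*Protocol article*

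**What the plan says.** The programme is "a 24-session-long stimulation program" (Abstract). Under 2.4 Procedure, children who cannot make up a missed session in the same week move on: "they will skip that session and continue with the normal session planned for the following week, but the missed session will be registered as lost". Its main stated reason is that "sometimes access to schools or a stable internet connection will not be guaranteed in the context of the study". A further reason is that the team will afterwards be able to "analyze the percentage of completion for each participant and determine the minimum completion percentage to ensure" effectiveness.

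Three other places bear on this:

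- Section 2.1.3 expects high dropout "due to the difficult living conditions in the proposed recruitment areas (gang violence, long distances from residences to school centres, etc".
- The Introduction states that "Living conditions during childhood and adolescence affect the cognitive and emotional development of minors".
- Section 2.3.2 says of the comparison arm: "The control group will use the time dedicated for intervention sessions to carry out a reading motivation program".

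Section 2.5 sets out an ANCOVA of post-score on pre-score, with optional covariates. It does not mention completion. Its contrast of normative and non-normative children is described as something to explore; the completion threshold in 2.4 carries no such label.

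**The concern.** A completion level that ensures effectiveness is a causal claim: children who reach it benefit because they reached it. The design randomises condition, by whole class. It does not randomise how many sessions a child in a programme class completes.

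Children with high completion may differ from the rest in school, connectivity and home circumstances, and the protocol itself says living conditions affect cognitive and emotional development. If those differences also affect change between T1 and T2, children with high completion will do better whether or not the programme does anything. Looking for the cut-off at which an effect appears adds a second problem, because the cut-off is then chosen on the outcome.

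What is at stake is a secondary conclusion, but one that others could use. Sections 3 and 4 foresee curricular use and transfer to other settings if the programme succeeds, and a stated minimum dose is something implementers could adopt.

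**Working it through.** **1. The plan's own figures.** For d = 0.3, with two-sided alpha 0.05 and power 0.80 assumed (the article states neither), an exact two-sample t calculation gives 176 per arm, 352 in total, power 0.801. This matches section 2.1.3. For dropout, 1 − 352/480 = 26.7%, which agrees with slightly more than 25%. The completion analysis has no figure in the article to reproduce.

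**2. Spurious gap above median completion, no true effect.** Let rho be the correlation between completion propensity and the T1-adjusted outcome in SD units. With both normal, the expected outcome above the median is rho × √(2/π) = rho × 0.798:

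- rho 0.1: 0.08 SD
- rho 0.2: 0.16 SD
- rho 0.3: 0.24 SD

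The design target is 0.3. This result does not depend on how completion is distributed.

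**3. Chance that some cut-off looks effective, no true effect.** Assumptions: 180 children per arm; adjusted outcome standard normal in both arms; treated children above each of six cut-offs (25, 40, 50, 60, 70, 80% completion) compared with all controls; a hit is p < 0.05 in the programme's favour. Two completion distributions bracket the answer.

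| rho | mean completion 80% (Beta(8,2)) | completion spread evenly |
|---|---|---|
| 0.1 | about 9% | about 20% |
| 0.2 | about 21% | about 45–47% |
| 0.3 | about 41% | about 75% |

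At rho = 0 the rate is about 5 to 6%, against a nominal 2.5% in the favourable direction. Most of the excess therefore comes from confounding rather than from trying several cut-offs. The comparison by allocated class stays at 2–3%.

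**4. Does T1 adjustment rescue it?** A second simulation used 176 per arm, pre/post correlation 0.6, completion averaging roughly 80% of 24 sessions and seven thresholds from 50 to 90%. It adjusted explicitly for the pre-score and let completion correlate rho both with the pre-score and with the part of the post-score that the pre-score does not explain. At rho 0.1, 0.2 and 0.3:

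- Treated above the threshold versus all controls: 13%, 28%, 52% with at least one hit.
- Above versus below among treated children only: 36%, 76%, 97%.

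Adjustment removes only the part of the confounding that runs through the T1 score.

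**5. A complier-average analysis at a fixed cut-off.** This respects randomisation but assumes no benefit below the cut-off. Suppose benefit is proportional to sessions (0.3 SD at full completion) and completion follows Beta(8,2), mean 0.8. The effect by allocation is 0.3 × 0.8 = 0.24 SD.

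- Cut-off 80%: 56.4% of children reach it, so the estimate is 0.24/0.564 = 0.43 SD. Their mean completion is 0.886, so their true effect is 0.3 × 0.886 = 0.27 SD.
- Cut-off 90%: 22.5% reach it, so the estimate is 0.24/0.225 = 1.07 SD. Their mean completion is 0.938, so their true effect is 0.28 SD.

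With sessions as a continuous exposure, 0.24/0.8 = 0.30 SD, which recovers the assumed effect of full completion.

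**The case against.** The strongest reply is that the article describes very little: one clause, offered as a supplementary reason for a logistical rule. It names no comparator, no search over cut-offs, no model and no test, and such details commonly sit in an analysis plan, which is not shown. That stands. The comparison with all controls and the cut-off search above are assumptions made to show scale. What remains is the stated aim, which is causal and which observed completion alone cannot deliver.

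A reader might infer that missed sessions reflect self-selection. The documents do not support that. Section 2.4 attributes them to school access and internet, which children do not choose, and the violence and distance in 2.1.3 are given as reasons for dropout, not for missed sessions. The link from living conditions to attendance is therefore probable rather than stated. School and connectivity are still not randomised.

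There are mitigating features. Missed sessions should be made up in the same week. Socioeconomic level and exposure to violence are measured (2.3.1), and section 2.5 allows covariates and multiplicity corrections. Covariates reduce confounding without guaranteeing its removal; multiplicity corrections address only the number of cut-offs. The crossover means completion is eventually observed in both groups, but never by random assignment.

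A reader might also infer that the trial's efficacy result is compromised, or that a threshold will certainly be carried into roll-out. Neither follows. The ANCOVA by allocated class does not use completion, and the transfer plans are conditional on effectiveness and mention no threshold.

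**Conclusion.** The point holds as a flaw in a stated secondary aim. The plan cannot validly determine a completion percentage that ensures effectiveness, because completion is observed rather than assigned and its likely drivers are related to the outcomes. The main comparison by allocated class is unaffected.

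The size is illustrative. The article gives neither rho nor the distribution of completion, and the false-finding rates roughly double between high and evenly spread completion. At rho 0.1 the spurious gap is about a quarter of the design target; at 0.3 it is about four-fifths. The simulations also ignore class clustering. The correction is worth making because it is cheap and because a minimum-dose statement is easily taken at face value.

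**What to change.** - In 2.4, replace the aim of determining a minimum percentage that ensures effectiveness with an exploratory, hypothesis-generating description of completion.
- Base all effectiveness conclusions on all children by allocated class.
- Fix any completion levels to be examined before T2 data are seen. Adjust for T1 score, school, socioeconomic level and exposure to violence, all of which are already collected.
- If a causal dose question is kept, use class allocation as the instrument and the number of sessions completed as a continuous exposure, stating the linear-dose assumption. If a cut-off version is used instead, state that it assumes no benefit below the cut-off and overstates the effect otherwise.
- Optionally, log attendance at the control sessions, which use the same time slot, so that children with similar attendance can be compared as exploratory support.

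The cost is a change of wording and, if the option is taken, an attendance sheet in control classes. An instrumental-variable estimate has wider intervals, and the team gives up a definitive minimum-dose claim.
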